## Data Management and Results

### Data Quality

A computerized database is used to collect and organize all data. Data is collected without personal identifying information using a code assigned by the assessor and researchers will only have access to this information in case of an incident. Data from all participants will be collected regardless of whether the participant withdraws from the intervention or not. Assessments, individual reports and databases will be double-checked. We will follow Data Quality Assessment Checklist and Recommended Procedures (DQA; USAID, 2014) that assesses a variety of dimensions as validity, reliability, timeliness, precision and integrity. Regarding interventions parameters, we will assess the coherence between personal diaries, phone-call follow-ups and actimeter. We will analyze if compliance is related to expected physical changes. In addition, if we identify any issues, we will inform and apply any required statistical procedures to control them.

### Outcomes

#### Primary Outcomes

To address the primary hypothesis, an extensive neuropsychological battery was designed by Projecte Moviment. Each test has been selected for its psychometric qualities and high relevance in the area of study. These tests provide measures of multiple functions: executive functions, visuospatial abilities, memory, language, attention and processing speed. We will calculate z-score composites from normalized raw data for each cognitive domain and a global cognitive function score as a sum of all domains (Table 3).

**TABLE 3 T3:** Primary outcomes: variables and measures.

**Outcome/Variable**			**Outcome measure**
**Composites 1st level**	**Composites 2nd level**	**Tests – Subtest**	
**Executive function**	Inhibition	Stroop – Interference	*Z* score
	Working memory	WAIS III – Backward span	*Z* score
		TMT – B	*Z* score
	Fluency	Letter fluency	*Z* score
		Category fluency	*Z* score
**Visuospatial function**	Visuospatial	ROCF – Copy accuracy	*Z* score
**Memory**	Verbal memory	RAVLT – Total learning	*Z* score
		RAVLT – Recall II	*Z* score
	Visual memory	ROCF – Memory accuracy	*Z* score
**Language**	Language	WAIS III – Vocabulary	*Z* score
		BNT (15 items)	*Z* score
**Attention – Speed**	Attention	WAIS III – Forward span	*Z* score
		WAIS III – Digit symbol coding	*Z* score
		WAIS-III – Symbol search	*Z* score
	Speed	TMT – A	*Z* score
		ROCF – Copy time	*Z* score

*Stroop test (Golden, 2001); WAIS-III, Wechsler Adult Intelligence Scale (Wechsler, 2001); TMT, Trail Making Test (Tombaugh, 2004); Verbal fluency tests (Peña-Casanova et al., 2009); ROCF, Rey-Osterrieth Complex Figure (Rey, 2009); RAVLT, Rey Auditory Verbal Learning Test (Schmidt, 1996; Marqués et al., 2013); BNT, Boston Naming Test (Goodglass et al., 2001).*

#### Secondary Outcomes

Several domains are assessed to test secondary hypotheses. Main outcomes and measures are described in Table 4.

**TABLE 4 T4:** Secondary outcomes: variables and measures.

	**Variable/Outcome**	**Outcome measure**
**General cognitive function**	Montreal Cognitive Assessment 5-min (MoCA 5-min)	*Z* score
	Mini-mental State Examination (MMSE)	*Z* score
**Psychological health Daily activity**	Geriatric Depression Scales (GDS-15)	*Z* score
	Modified version of Visual Analog Mood Scale (VAMS)	*Z* score
	Short Informant Questionnaire on Cognitive Decline in the Elderly (S-IQCODE)	*Z* score
	Pittsburg Sleep Quality Index (PSQI)	*Z* score
	Clinical Outcomes in Routine Evaluation-Outcome Measure (CORE-OM)	*Z* score
**Fitness**	Cardiorespiratory fitness (Rockport 1-mile walk test)	VO_2_ max
**Physical activity**	Reduced Minnesota leisure time physical activity questionnaire (VREM)	METs
	Actimeter activity parameters (Polar Loop^®^)	Hours, steps, km, kcal
	Actimeter sleeping parameters (Polar Loop^®^)	Hours, %
**Health status**	Weight, height, and waist diameter	Kg, cm
	Blood pressure	mm Hg
	Hypertension, diabetes, and dyslipidemia	Yes/No
	Tobacco and alcohol use	Yes/No, Units
**Blood sample data**	Hemogram	Conventional units
	Biochemistry in plasma	Conventional units
	Cortisol	ng/mL
	Genetics – Apolipoprotein E (APOE)	E4+/E4-
	Genetics – Brain Derived Neurotrophic Factor (BDNF)	Met+/Met-
	Cytokines	ng/mL
**Neuroimaging**	T1-weighted	Volume
	T2-weighted turbo inversion	Volume
	Susceptibility weighted imaging	Volume
	Resting state	*Z* score
	Diffusion tensor imaging (DTI)	Fractional Anisotropy Index

*MoCA 5-min (Wong et al., 2015); MMSE (Blesa et al., 2001); GDS-15 (Martínez et al., 2002); VAMS (Stern et al., 1997); S-IQCODE (Morales et al., 1992); PSQI (Rico and Fernández, 1997); CORE-OM (Trujillo et al., 2016); Rockport 1-mile walk test (Kline et al., 1987); VREM (Ruiz et al., 2012); MET (Metabolic Equivalent of Task).*

##### Cognitive decline screening

Montreal Cognitive Assessment 5 min (Wong et al., 2015) and Mini-Mental State Examination (Blesa et al., 2001) assess global cognitive function as relevant markers of cognitive decline.

##### Psychological health and daily activity

Questionnaires ask for depressive symptoms and emotional status, sleep quality and subjective performance in daily activities. These outcomes will test the potential effect of the interventions to enhance perceived psychological status and functionality which may be related to cognitive effects and other secondary outcomes.

##### Aerobic fitness

CRF is assessed by the Rockport 1 mile walk test. Participants are instructed to walk on a treadmill for 1 mile adjusting their speed in order to be as fast as possible without running (Technogym^®^, Italy). Maximal aerobic capacity (VO2 max) will be estimated with the linear regression reported by Kline et al. (1987). CRF estimation is a well-known measure of cardiovascular health. We expect to describe the relationship between CRF and the physiological blood measures as well as how change in CRF relate to brain and cognitive outcomes.

##### Physical activity

Information about energy expenditure of PA performed during the last month is obtained by the Reduced Minnesota leisure time PA questionnaire (Ruiz et al., 2012). Polar Loop^®^ actimeter (Polar Electro, NY, United States) registers daily PA (hours, steps, km, kcal) and sleeping (hours, %) parameters. Energy expenditure is the very first consequence of exercising. We aim to identify if baseline energy expenditure is related to baseline CRF and describe how the change in energy expenditure is related to physiological molecular correlates, CRF and to brain and cognitive outcomes.

##### Health status

A nurse registers demographic data, blood pressure, anthropometrics measurements, and cardiovascular risk factors. Demographic data will allow us to control the influence of individual variables. We expect that weight loss could be related to the physiological blood markers and to primary outcomes or other secondary outcomes. The reduction of cardiovascular risk factors is an indirect measure of better cardiovascular health that has been related to exercise.

##### Blood-sample data

Hemogram, biochemical parameters, and lipidic profile will be quantified in a common blood test. Cortisol will be analyzed in plasma and genetic biomarkers in APOE (SNPs rs429358 and rs7412) and BDNF (rs6265) genes will be determined in the buffy coat fraction. Finally, a set of 105 cytokines will be studied semi-quantitatively with The Proteome Profiler Human^TM^ XL Cytokine Array (R&D Systems, MN, United States). Biomarkers with relevant differences within and between groups will be analyzed quantitatively using an ELISA immunoassay method. We have chosen relevant genetic variables and physiological molecular markers that have been related to exercise interventions. We expect to detect changes at 3 months and describe any type of relationship with cognitive outcomes.

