**Methods:**

One hundred and forty healthy physically inactive older adults will be randomly assigned to computerized cognitive training (CCT), aerobic exercise (AE), combined training (COMB), or a control group. The intervention consists of a 3 month home-based program 5 days per week in sessions of 45 min. Data from cognitive, physical, and psychological tests, cardiovascular risk factors, structural and functional brain scans, and blood samples will be obtained before and after the intervention.

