1.All intervention conditions will positively impact psychological and subjective daily functional performance assessed by questionnaires compared to controls.2.Aerobic exercise and COMB will similarly increase CRF and energy expenditure in daily activity compared to cognitive and control conditions.3.All intervention conditions will positively impact the structure and function of the brain assessed by whole brain analyses, structures of interest and white matter lesions volume and microstructure, cortical thickness and functional connectivity compared to a control group.4.Aerobic exercise and COMB will improve immunity, reduce inflammation and improve vascular risk factors compared to cognitive and control conditions.5.Individual variables (i.e., sex, age, cognitive baseline, CRF baseline) will predict the effect of the interventions on cognition.6.Changes in cognition will be related to specific changes in secondary outcomes depending on the intervention.

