## Methods

### Study Oversight and Schedule

Projecte Moviment is a multi-center, single-blind randomized controlled trial that started November 2015 with the aim of recruiting 140 participants distributed in four parallel groups (one control group, *n* = 20; three intervention groups, *n* = 40 each). All participants give their written informed consent and are assessed at baseline and 3 months later, immediately after the intervention (Figure 1). This study is led by the Faculty of Psychology of the University of Barcelona in collaboration with Institut Universitari d’Investigació en Atenció Primària Jordi Gol, Hospital Germans Trias i Pujol and Institute Guttmann; it was approved by the responsible ethics committees following the Declaration of Helsinki.

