#### Statistical Analyses

Addressing the primary objective, statistical procedures will be performed with IBM SPSS Statistics 24 and R Environment. The distribution of raw scores will be examined in order to assess data quality (i.e., outliers, skewness) and we will obtain sample *z*-scores for all cognitive tests. Five primary domains will be calculated by adding *z*-scores – executive function, memory, language, attention-speed, and visuospatial function – which will be split into nine secondary domains in order to assess specific changes within each domain – inhibition, fluency, working memory, verbal memory, visual memory, language, attention, speed and visuospatial function (see Table 3). Domains will be based on the literature (Strauss and Spreen, 1998; Lezak et al., 2012) given the fact that a principle component analysis would not be appropriate for our sample size.

In order to test our primary hypotheses, we will conduct an intention-to-treat (ITT) analysis considering data from all randomized participants, including those that complete and drop-out, in order to prevent attrition bias. An adequate method of imputation will be applied and informed. Parametric or non-parametric tests will be chosen regarding the fitting of data to statistical requirements of the tests and we will follow a coherent pipeline to explore variance: (a) comparison of baseline values between groups to identify potential variables to adjust further analyses; (b) comparison of variables at different time-points for each group to identify the independent effect of each condition; (c) identification of significant cross-time correlations in order to determine whether it is necessary to control for baseline measures; (d) interaction between conditions and time-points to compare interventions. Sex, age, and years of education will be considered covariates beforehand and a two-tailed *p*-value < 0.05 will be set as the significant threshold and the corresponding correction for multiple comparisons will be applied. In a second phase, we will define a per-protocol (PP) sample including only subjects that finished the intervention with at least 80% adherence and we will reproduce the same pipeline. In case of high disparity between ITT and PP results, we will analyze potential variables related to that discrepancy.

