We will analyze our secondary hypotheses following the same pipeline in the per-protocol sample to guarantee that we will be studying the effects of the intervention on the previously described outcomes. We will examine potential mediator effects through relationships between primary and secondary outcomes accounting for the intervention condition using adequate correlational methods and linear mixed models. Structural neuroimaging data will be first processed studying whole brain, hippocampus and frontal lobe volumes and white matter microstructure. In a second phase, connectivity and white matter lesions will be analyzed. Data will be published in several papers where detailed procedures and software packages will be described.

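### Cytokines are chosen for ELISA on the trial's own group differences, and no stated correction counts the 105-marker search, so results for the chosen markers lean towards the array result

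*Protocol article*

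**What the plan says.** Under Blood-sample data, the protocol article says that "a set of 105 cytokines will be studied semi-quantitatively", and gives the rule for the next stage: "Biomarkers with relevant differences within and between groups will be analyzed quantitatively using an ELISA immunoassay method". It does not define which differences count as relevant. The only blood it describes is the participants' own; the abstract says that "blood samples will be obtained before and after the intervention". Table 4 lists the cytokine outcome in ng/mL.

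Secondary hypothesis 4 (Aims of the Study) uses these data comparatively: aerobic exercise and combined training "will improve immunity, reduce inflammation and improve vascular risk factors compared to cognitive and control conditions". Blood-sample data also plans to relate the markers to cognitive outcomes.

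Under Statistical Analyses, a "two-tailed *p*-value < 0.05 will be set as the significant threshold", and "the corresponding correction for multiple comparisons will be applied". For the rest: "We will analyze our secondary hypotheses following the same pipeline in the per-protocol sample". That pipeline contains a pre–post comparison within each group (step b) and a condition-by-time interaction (step d). Neither section says whether the correction governs the choice of markers from the array, or whether later ELISA tests account for all the markers screened.

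**The concern.** A marker goes forward because its groups differ in this sample. Part of any such difference is chance: which people happened to be in which arm, and how they happened to change. Measuring the same people again with a better assay reproduces that part. ELISA results for selected markers are thus conditional on a favourable array result, but an ordinary p-value and effect estimate ignore the condition.

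This matters because a semi-quantitative array would not supply values in ng/mL. Quantitative inference on cytokines therefore falls on the ELISA stage, that is, on markers already selected on outcome. A statement that exercise reduces inflammation, and any later link between those markers and cognition, would inherit the selection.

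A second issue is the within-group part of the rule. Change within one arm can come from season, assay batch or regression to the mean. Hypothesis 4 is about differences between arms, and within-arm change does not bear on it.

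**Working it through.** The article states no error rate or threshold for this step, so there is no figure of its own to reproduce. The calculations below are illustrations.

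**Inputs from the document.** 105 markers (Blood-sample data); two-sided 0.05 (Statistical Analyses); "one control group, *n* = 20; three intervention groups, *n* = 40 each" (Study Oversight and Schedule).

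**Assumptions.** No true effects; array selection at uncorrected p<0.05; array and ELISA test statistics bivariate normal with correlation ρ. The document gives no ρ, so a range is shown.

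**1. Chance selections per contrast.** 105 × 0.05 = 5.25.

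**2. Distinct null markers selected.** A simulation under the null with arms of 20/40/40/40, four within-group tests and six pairwise between-group tests gives, out of 105:
- about 13 if a marker needs both a within- and a between-group difference;
- about 27 if either is enough.

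**3. Carry-over to ELISA.** For a null marker selected on the array, the chance of ELISA p<0.05 in the same direction is 2 × Φ₂(−1.96, −1.96; ρ) / 0.05, where Φ₂ is the bivariate normal distribution function. The mean ELISA z in the selected direction is ρ × φ(1.96) / 0.025, with φ the normal density. For the Bonferroni column the ELISA cut-off is 0.05/5 = 0.01 two-sided, as if five selected markers were tested and only those five counted.

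| ρ | Repeat at p<0.05 | Expected per contrast (5.25 × repeat) | Repeat, Bonferroni over 5 | Mean ELISA z |
|---|---|---|---|---|
| 0 (independent sample) | 2.5% | 0.13 | 0.5% | 0 |
| 0.5 | 18.5% | 0.97 | 5.6% | 1.17 |
| 0.7 | 33.1% | 1.74 | 10.6% | 1.64 |
| 0.8 | 43.9% | 2.30 | 14.1% | 1.87 |
| 0.9 | 59.3% | 3.11 | 18.1% | 2.10 |

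Between ρ = 0.5 and 0.9 a chance finding repeats about 7 to 24 times as often as in independent participants (18.5/2.5 = 7.4; 59.3/2.5 = 23.7). Correcting over the selected markers alone reduces this but does not remove it. The mean z column shows the effect-size bias: a marker with no effect has an expected ELISA statistic of 1.2 to 2.1 rather than 0.

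**4. If all 105 markers are counted.** For one contrast the threshold is 0.05/105 = 0.000476, and the expected chance selections are 105 × 0.000476 = 0.05 instead of 5.25. If that threshold is applied when ELISA values are tested, the expected number of false claims per contrast is also at most 0.05, whatever ρ is.

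**5. Within-group change.** Suppose a drift common to all arms of 0.4 SD of the change score (assumed). A paired t-test at 0.05 has noncentrality 0.4 × √n: 2.53 at n = 40 and 1.79 at n = 20. It flags the drift with probability about 69% in an intervention arm and about 40% in the control arm. A drift with no treatment effect would thus be flagged more often in an intervention arm, only because that arm is larger.

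**The case against.** The strongest reply is that the text describes a screen followed by quantification and claims nothing more. That stands. A reader might infer that the plan presents ELISA as confirmation of the array, but the article never uses that idea; it says only that selected markers are measured quantitatively. That the participants are the same is also an inference, though the document describes no other blood.

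A correction for multiple comparisons is stated and carried to the secondary hypotheses. If it covered the array step, chance selections would fall to 0.05 per contrast. The article may leave its method to a fuller document. But the array criterion is relevance, not significance, and a natural reading of the two sections corrects only the tests done on markers that reach ELISA.

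Two stronger readings are not supported. One is that most chance findings will repeat on ELISA: the calculation puts this above one half only as ρ nears 0.9, and ρ is unknown. The other is a total of about 37 false hits, from three control contrasts (15.75) plus four within-group tests (21). That sum counts a marker flagged twice as two, assumes no correction, and treats within-group change as sufficient by itself, although the wording can equally require both kinds of difference.

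Hypothesis 4 also draws on outcomes not chosen through the array, such as blood pressure, lipids and cortisol, and the condition-by-time interaction remains the planned basis for comparing arms. Both points limit the reach of the problem; neither removes the selection of cytokines.

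**Conclusion.** The point holds in a limited form. Selecting markers on the trial's own group differences and then testing them in what can only be the same participants biases their p-values and effect sizes towards the array result, and the stated correction is not tied to the search over 105 markers. The direction of the bias holds for any positive array–ELISA correlation. Its size (an 18.5% to 59% repeat rate against 2.5%) rests on an assumed p<0.05 screen and an assumed correlation of 0.5 to 0.9. The objection to within-group change applies only if such change alone can qualify a marker, which the wording leaves open.

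This is more than an omitted detail, because the selection rule is written into the article and feeds a comparative hypothesis. It concerns one secondary component and leaves the primary cognitive analysis untouched. It should be corrected before the cytokine data are analysed.

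**What to change.** Amend Blood-sample data, with a matching sentence in Statistical Analyses:

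- Select ELISA targets on the baseline-adjusted between-arm difference in change, with the contrasts and the threshold stated.
- Do not let within-group change alone qualify a marker.
- Make the multiplicity family for any cytokine claim all 105 screened markers and the contrasts used, including when ELISA values are tested.
- Report ELISA as quantification of selected markers, not as independent evidence, and note that the effect sizes are subject to selection.

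The array p-value need not become the inferential result; testing the ELISA values is acceptable if the whole search is counted. Counting it does not remove the bias in effect size, which is why the caveat in the last item is needed.

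The cost is wording only, with no new data, visits or assays. The downside is that fewer markers go forward.

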##### Neuroimaging

Magnetic Resonance Imaging will be obtained in a Siemens Magnetom Verio Symo MR B17 (Siemens Healthineers, Erlangen, Germany). The protocol includes: (1) T1-weighted multi-planar reformat sequence (voxel: 0.9 × 0.9 × 0.9 mm, TR/TE: 1900/2.73 ms, slices: 192; thickness: 0.9 mm); (2) T2-weighted turbo spin-echo sequence (voxel: 0.7 × 0.5 × 3 mm, TR/TE: 6000/74 ms, slices: 35, thickness: 3 mm); (3) T2-weighted turbo inversion recovery magnitude (voxel: 1 × 0.8 × 3 mm, TR/TE: 9000/99 ms, slices: 44, thickness: 3 mm); (4) Susceptibility-weighted imaging with T2 – fl3d sequence (TR/TE: 28/20 ms, slices: 88); (5) Resting state imaging with a gradient echo planar imaging sequence (TR/TE: 2000/25 ms, slices: 39, thickness: 3 mm, volumes: 240); (6) Diffusion tensor imaging, echo planar imaging (voxel: 2 × 2 × 2 mm, TR/TE: 10200/89 ms, 64 directions, 1 acquisition). On one side, structural and functional brain outcomes may help identify the molecular changes that are related to changes in brain volume, microstructure and connectivity between groups. On the other, we aim to identify if changes in the MRI outcomes are associated with cognitive changes.

Other parameters from the follow-up such us adherence and type of adverse events will be described.

### Analyses

#### Power Analysis

The sample size was determined considering previous studies (Erickson et al., 2011) and the effect size and the standard error of cardiovascular interventions on all cognitive tasks reported in a previous meta-analytic study (Colcombe and Kramer, 2003). We also considered the following assumptions: bilateral contrasts and an effect size of 0.4 using the Tukey–Kramer multiple comparison test at 0.05 significance level with a common standard deviation within a group of 0.3. In order to have at least 80% statistical power to answer the 3 primary aims of the project, we need 18 subjects in the control group and 36 for CCT, AE, and COMB groups, respectively. Assuming 10% of lost to follow up (Rahe et al., 2015), we need a total sample size of 139 subjects (control group *n* = 19, intervention groups *n* = 40). Sample power has been computed using PASS 14 Power Analysis and Sample Size Software.

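### The stated 80% power for an effect size of 0.4 does not hold on the z-score scale of the primary outcomes, where 18 versus 36 participants detect about 1.0 SD unadjusted

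*Protocol article*

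**What the plan says.** The Power Analysis section says that the sample size took account of previous studies and of "the effect size and the standard error of cardiovascular interventions on all cognitive tasks reported in a previous meta-analytic study". It then lists further assumptions. Testing is two-sided, and the remaining inputs are given as: "effect size of 0.4 using the Tukey–Kramer multiple comparison test at 0.05 significance level with a common standard deviation within a group of 0.3". The resulting requirement is 18 evaluable participants in the control group and 36 in each of the three intervention groups. The purpose is given as follows: "In order to have at least 80% statistical power to answer the 3 primary aims of the project".

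The Primary Outcomes section and Table 3 put every cognitive test on a z-score. Under Statistical Analyses these are sample z-scores, and the domains are sums: "Five primary domains will be calculated by adding" the z-scores of their tests. In Table 3, executive function and attention-speed have five tests each, memory has three, and visuospatial function has one.

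Control for baseline is conditional under Statistical Analyses: it depends on whether cross-time correlations turn out to be significant. The article gives no pre-post correlation and no change-score SD.

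**The concern.** A sample z-score has an SD of 1 by construction, and a sum of positively correlated z-scores has an SD above 1. An SD of 0.3 fits neither. If 0.4 is a difference on a scale with SD 0.3, the trial was planned for 1.33 SD. If 0.4 is meant in SD units, the SD of 0.3 should not enter at all. The paragraph does not say which is meant.

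The stake is how a null result is read. The Discussion itself notes that null results are possible in healthy and middle-aged participants. A reader told that the trial had 80% power for an effect size of 0.4 would take a null result as evidence against effects of that size, although the design reliably detects only much larger ones.

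**Working it through.** **Inputs from the article.** Four groups; 18 control and 36 per intervention (126 evaluable); two-sided Tukey–Kramer at 0.05; effect 0.4; SD 0.3; power at least 80%.

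**Formula.** For one intervention-versus-control contrast with standardised difference d:
- error df = 126 − 4 = 122
- critical value = q(0.95; 4, 122)/√2 = 2.605
- noncentrality = d/√(1/18 + 1/36) = 3.464 d
- power from the noncentral t distribution

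**Step 1: the plan's figure, read literally.** d = 0.4/0.3 = 1.333 and noncentrality = 4.619. Power is 97.7% per contrast and, by simulation, 94.8% for all three contrasts together. That satisfies a target of at least 80%, but 18/36 is then not the size needed: 10/20 gives 78.7% and 11/22 gives 83.3% per contrast, and 13/26 gives about 81% for all three.

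**Step 2: the plan's figure, with 0.4 read as Cohen's f.** Take allocation 1:2:2:2 and three equal intervention means. Then f = d·√(1/7 × 6/7) = d·√(6/49), so d = 0.4/0.350 = 1.143. Simulated power for all three control contrasts together is about 79% at 17/34 and about 82% at 18/36. This reproduces the stated sizes. Because f is dimensionless, the SD of 0.3 cancels, and the planned difference is 1.14 SD.

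**Step 3: what 18/36 detects.** Solving for 80% power per contrast gives d = 0.997. At d = 1.0, power is 80.3%.

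**Step 4: power at 0.4 SD, unadjusted.** Noncentrality = 3.464 × 0.4 = 1.386, and power is 11.6% per contrast. With no multiplicity correction it is about 28%. For all three contrasts together it is 3.5%.

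**Step 5: baseline adjustment.** The article gives no pre-post correlation ρ, so the values below are assumptions. The residual SD is √(1 − ρ²), which raises d to 0.4/√(1 − ρ²) and lowers the detectable difference to 0.997·√(1 − ρ²).

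| Assumed ρ | Power at 0.4 SD | Difference for 80% power |
|---|---|---|
| 0 (unadjusted) | 12% | 1.00 SD |
| 0.5 | 16% | 0.86 SD |
| 0.7 | 26% | 0.71 SD |
| 0.8 | 39% | 0.60 SD |
| 0.9 | 72% | 0.43 SD |

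Power of 80% at 0.4 SD needs ρ = √(1 − (0.4/0.997)²) = 0.92.

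**Step 6: could 0.3 be a residual or change SD?** For a residual, √(1 − ρ²) = 0.3 gives ρ = 0.954. For a change score, √(2(1 − ρ)) = 0.3 gives ρ = 0.955. These hold for an outcome with SD 1; a sum with a larger SD would need a higher correlation still.

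**Step 7: the scale of the composites.** A sum of k z-scores with common correlation r has SD √(k + k(k − 1)r). At assumed r of 0.3 to 0.5 this is 2.19 to 2.45 for three tests and 3.32 to 3.87 for five. A raw difference of 0.4 on a scale with SD 2 is 0.2 SD, with power of 3%. If the z-scores were averaged instead, the SD would be about 0.7 to 0.8 for three or five tests (0.66 to 0.82), and power at a raw 0.4 would lie between 15% (SD 0.9) and 39% (SD 0.6). The result at 0.4 SD in Step 4 does not depend on this choice.

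**The case against.** The strongest defence is Step 2. The stated test is Tukey–Kramer, the stated goal is to answer three aims, and 0.4 read as f gives 18/36 as the smallest 1:2 size with at least 80% power for all three contrasts. This stands, so it cannot be said that the sample size is irreproducible. It does not rescue the power statement. The article never calls 0.4 an f, it specifies an SD that this reading does not use, and the implied difference is above 1 SD. An omnibus F test with f = 0.3 also gives 80.3%, but the article names 0.3 as an SD and Tukey–Kramer as the test.

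A reader might infer that the authors took a pooled meta-analytic effect and its standard error, used the latter as an SD, and so standardised twice. The article mentions that source and then lists 0.4 and 0.3 as further assumptions. It does not say that either number is the meta-analytic figure, so this remains a guess about origin.

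A reader might also take 12% as the trial's power. That is the case without baseline adjustment. The planned analysis includes a condition-by-time interaction, sex, age and education as covariates, and possible control for baseline, so actual power at 0.4 SD may be well above 12%.

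Finally, each primary hypothesis names three or four composites while the calculation covers one outcome. Calculating power per outcome is normal practice, a multiplicity correction is promised, and its detail may sit in an analysis plan. It is enough to label the figure as per composite.

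**Conclusion.** The concern holds in this form: the article leaves both 0.4 and 0.3 undefined, and on the scale of the primary outcomes the design does not give 80% power at 0.4 SD. On every reading tried, 80% Tukey–Kramer power per contrast at 18 versus 36 requires a true difference of about 1.0 SD unadjusted. At 0.4 SD, power is about 12% unadjusted and 16% to 72% at assumed pre-post correlations of 0.5 to 0.9, reaching 80% only near 0.92. The unadjusted figures rest only on the article's sample sizes and test. The adjusted figures rest on correlations that the article does not supply. The documents do not support the stronger claims that the sample size cannot be reproduced or that a standard error was used as an SD.

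**What to change.** In the Power Analysis section:

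- State what kind of effect size 0.4 is: a raw difference, a standardised difference, or f.
- State the scale on which the SD of 0.3 holds, with the pre-post correlation and its basis if it is a change or residual SD. If the calculation used f, remove the SD and give the implied difference.
- Replace the 80% statement with the detectable difference on the z-score scale, per composite and per contrast. For example: with 18 control and 36 intervention completers, 80% power (Tukey–Kramer, two-sided 0.05) requires a true difference of about 1.0 SD unadjusted, or about 0.7 SD and 0.6 SD with baseline adjustment at assumed pre-post correlations of 0.7 and 0.8.
- If power at 0.4 SD is reported, give the whole range (12% unadjusted; 16%, 26%, 39% and 72% at correlations of 0.5, 0.7, 0.8 and 0.9) and label the correlations as assumptions.

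This rewords one paragraph. It needs no new data and no extra enrolment. The only cost is a less favourable stated figure.
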